### Outcome assessments

The assessors are blinded to grouping. The primary outcome will be all cases of recurrent stroke over a follow-up period of 9 months after receiving 12-week acupuncture treatments. Secondary endpoints, such as 24-h ambulatory BP, TCM syndrome score, Short Form 36-item Health Survey (SF-36) results, National Institute of Health Stroke Scale (NIHSS) and Barthel Index (BI) scale scores will be assessed at baseline, 6 weeks, and 12 weeks post initiating treatments; serum nitric oxide (NO), endothelin (ET), homocysteine (Hcy), soluble CD40 ligand (sCD40L), and copeptin levels and cardiac ultrasound, carotid artery ultrasound, transcranial Doppler, and lower extremity ultrasound results will be evaluated at baseline and 12 weeks after treatment. Other safety indicators including baseline general physical examination, blood, urine, and stool routine tests, coagulation function, D-dimer level, liver and kidney function, electrocardiograph as well as a chest X-ray will also be examined 12 weeks after randomization. At 6 months after randomization, blood, urine, and stool routine tests, coagulation function, D-dimer level, liver and kidney function, electrocardiograph, NO, ET, Hcy, sCD40L, and copeptin tests will be re-checked, with some hope of improving patients’ adherence to treatment. All-cause mortality will also be evaluated during the follow-up period. The Essen Stroke Risk Score (ESRS) will be additionally assessed at baseline and 1 year post randomization.

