### Sample size and statistical methods

The sample size calculation of the study was based on China’s Ministry of Health data suggesting that at least 197 patients are required in each group for the final analysis to achieve a power of 80% to demonstrate a recurrence rate of 7%, rather than 16% resulting from *HuoXueSanFeng* acupuncture (data not shown, please see Additional file 1), at a two-sided significance level of 5%. Given a projected dropout rate of 15%, we aimed to recruit 480 patients for the study.

Statistical analysis will be conducted by a third party who is unaware of the treatment allocation. Data will be analyzed with SAS 9.1 and SPSS 19.0 software packages. Two-sided *P* < 0.05 represents statistical significance for all the analyses. Both intention-to-treat analysis (ITT) and per-protocol (PP) analysis will be performed. We will compare the result of ITT analysis with that of PP analysis to determine whether the results are consistent. For the ITT analysis, missing data will be handled by Last Observation Carry Forward rules, in brief, the finally observed data will be used for replacement of the missing primary variables.

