Baseline demographic characteristics, including individual variables, such as age, sex, history of atrial fibrillation with or without current anti-coagulation medication, history of diabetes and smoking, and other baseline values, will be expressed with descriptive statistics for the two groups. For the primary outcome, recurrent stroke events, and secondary outcomes, the mortality rate and detailed causes (stroke or non-stroke), will be described as percentage (%), between-group difference will be analyzed using the chi-square test or Fisher’s exact test. For filling in the daily BP diary, it is required to measure BP four times each day at baseline before treatment, 2 weeks, 6 weeks, 12 weeks, 6 months, and 1 year after treatment. We will compare between-group or within-group values at the indicated time points. For highly effective use of the daily BP data, on one hand, we will collect all the values of the measurements at the same time in the day until each predesigned time point for comparison and, on the other hand, we will collate the four daily measurements to yield an average value in a day for later comparison at the time points mentioned above. Other secondary endpoints at different time points will also be compared. All the above different time-point assessments will be analyzed by repeated measures analysis of variance (ANOVA). Adverse events in each group will be documented as percentage (%) for safety assessments using the chi-square test or Fisher’s exact test.

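### Repeated-measures ANOVA is fixed for all serial secondary outcomes while the reach of the LOCF rule is unclear: patients with a missed visit are either deleted endpoint by endpoint or have values carried past dropout or death

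*Protocol article*

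**What the plan says.** All references are to the protocol article.

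- **Method.** Under Sample size and statistical methods, after the diary blood pressure (BP) comparisons and the other secondary endpoints measured over time: "All the above different time-point assessments will be analyzed by repeated measures analysis of variance (ANOVA".
- **Missing data.** The same section says: "For the ITT analysis, missing data will be handled by Last Observation Carry Forward rules". It then glosses this in short form: "the finally observed data will be used for replacement of the missing primary variables".
- **Primary outcome.** Outcome assessments: "The primary outcome will be all cases of recurrent stroke over a follow-up period of 9 months after receiving 12-week acupuncture treatments". This is an event, compared by chi-square or Fisher's exact test. Mortality is tested the same way. Neither enters the ANOVA.
- **Schedules.** On the timing of home readings: "it is required to measure BP four times each day at baseline before treatment, 2 weeks, 6 weeks, 12 weeks, 6 months, and 1 year". Ambulatory BP, the TCM syndrome score, SF-36, NIHSS and Barthel Index "will be assessed at baseline, 6 weeks, and 12 weeks post initiating treatments". Table 1 has the serum markers at baseline, week 12 and week 24.
- **Expected losses.** "Given a projected dropout rate of 15%, we aimed to recruit 480 patients for the study". Patient safety allows for withdrawal after a serious adverse event, all-cause death is recorded during follow-up, and the Discussion names compliance over the 9 months as a weakness.
- **Withdrawn patients.** Informed consent says that the data already available on them stay in the final analyses. The statistical section promises both intention-to-treat and per-protocol analyses.

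**The concern.** Classical repeated-measures ANOVA needs a full set of values for each patient. A patient with one gap is either left out of that endpoint or must have the gap filled first. The plan expects gaps, yet it spells out its filling rule only for primary variables, and the primary outcome is not in the ANOVA. The analyst therefore has two possible readings, and neither serves the trial well.

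Under the first, the diary BP comparison at weeks 2, 6 and 12 is restricted to patients who also supplied a 1-year value. Remaining in the study for a year is a post-randomisation event. The medication-adjustment rules differ between the arms, so those who remain need not be comparable. Under the second, a patient who dies or leaves is analysed at later visits with an old value treated as if it had been measured.

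BP is the pathway through which the article expects acupuncture to reduce recurrence, so the BP comparison will shape how any stroke result is interpreted.

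**Working it through.** **Step 1. The plan's own figure.** For 16% versus 7%, two-sided 5%, 80% power and pooled variance (mean rate 0.115):

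n = [1.96·√(2·0.115·0.885) + 0.8416·√(0.16·0.84 + 0.07·0.93)]² / 0.09² = (0.8843 + 0.3759)² / 0.0081 ≈ 196.1, so 197 per group.

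This reproduces the stated 197. Allowing for 15% dropout, 197/0.85 = 231.8, so 232 per group and 464 in total, which 480 covers. The sample size is sound and this point does not touch it.

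**Step 2. Does the named method delete attended visits?** In a small simulated data set of 20 subjects with 3 visits each, 3 subjects had the last visit removed, leaving 57 observations. A standard repeated-measures ANOVA routine refused the data as unbalanced. The complete-case version kept 17 subjects and 51 observations, so the 6 values that the three subjects did supply were lost. A mixed model used all 20 subjects and all 57 observations.

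**Step 3. Size if LOCF does not apply.** 15% of 480 = 72 patients (36 of 240 per arm), leaving 408. Deletion works endpoint by endpoint, so the loss depends on when each endpoint's last visit falls. The article does not give the timing of dropout. The table assumes a share f of it before week 12 and the rest spread evenly over weeks 12 to 48.

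- Endpoints ending at week 12: 72·f.
- Serum markers, ending at week 24: 72·f + 72·(1−f)·12/36.
- Diary BP to 1 year: 72, whatever f is.
- Patients with a week-12 diary value who are nevertheless deleted: 72·(1−f).

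| f (assumed) | Week-12 endpoints, lost | Serum markers, lost | Diary BP, lost | Week-12 diary value in hand but discarded |
|---|---|---|---|---|
| 0 | 0 | 24 | 72 | 72 |
| 0.25 | 18 | 36 | 72 | 54 |
| 0.50 | 36 | 48 | 72 | 36 |
| 0.75 | 54 | 60 | 72 | 18 |
| 1 | 72 | 72 | 72 | 0 |

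Even with purely random dropout, discarding week-12 values in hand costs precision. At most (f = 0) the standard error of the week-12 diary difference grows by √(240/204) = 1.085, about 8%.

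**Step 4. If LOCF does apply.** No one with an earlier value is deleted. Instead up to 72 of the 480 values at 1 year (15%) are carried forward but enter the ANOVA as measurements. For those who died, the carried value stands for a time at which no BP exists.

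**Step 5. The texts side by side.** Deleting attended visits does not fit an intention-to-treat analysis or the Informed consent undertaking on withdrawn patients' data. Carrying values forward keeps the patients, but adds values that were never observed.

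**The case against.** The strongest reply is that the LOCF sentence opens without restriction and that the reference to primary variables is only a gloss. There is a single binary primary outcome, so a plural and a carry-forward rule fit serial measures at least as well. On that reading patients are filled, not deleted. This stands as a possible reading, and deletion should not be asserted as fact. It does not rescue the plan, because ANOVA after LOCF has its own bias and understates uncertainty.

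A reader might infer that patients who leave are dropped from every secondary time point. The documents do not support that. A patient lost at month 10 has had the opportunity to complete every endpoint ending at week 12 or 24, and mortality lies outside the ANOVA. Even for the diary, the text speaks of collecting readings up to each time point, so someone lost at month 10 may still contribute to the 1-year value. Hence the wording up to about 72.

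A reader might also infer a bias in favour of acupuncture. One can construct it. With an SD of 12 mmHg, 15% dropout in both arms and BP-dependent dropout in the experimental arm only, the week-12 difference among completers shifts by about −0.4 to −1.6 mmHg for odds ratios of 1.28 to 2.7 per SD. Only the 15% comes from the article. The SD, the one-sided dependence and the placing of all dropout after week 12 are assumptions, and the reverse dependence would reverse the sign.

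Finally, the article names no software procedure, and such detail is commonly left to an analysis plan. That is fair as to the procedure. But the article does fix ANOVA by name, and it does state a missing-data rule whose scope cannot be determined.

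**Conclusion.** The point holds in limited form. The article fixes a complete-data method for all serial secondary outcomes and leaves unclear whether its LOCF rule reaches them.

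- **Without LOCF:** classical ANOVA excludes up to about 72 of 480 patients from diary BP to 1 year, and 0 to 72 from endpoints ending at week 12, depending on dropout timing. This is at odds with the intention-to-treat aim and with the Informed consent section.
- **With LOCF:** up to 15% of the 1-year values are carried past dropout or death.

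The direction and size of any resulting bias cannot be determined, since neither the timing nor the causes of dropout are given. The counts rest on the planned 15% and on the classical form of the ANOVA. The primary outcome, mortality and the sample size are unaffected. The change is worth making, but it concerns secondary outcomes only.

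**What to change.** Two edits under Sample size and statistical methods, which must be made together:

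1. Replace repeated-measures ANOVA with a likelihood-based mixed model for repeated measures, with treatment-by-time terms, unstructured covariance, all observed visits and no filled-in values. Report the arm difference at each time point.
2. State that LOCF does not apply to these outcomes. Otherwise the LOCF sentence would contradict the new model.

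Report deaths by arm beside each outcome, because the model on its own does not show who could not be measured. A sensitivity analysis for deaths on NIHSS and Barthel Index, for example by worst rank, is optional.

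The cost is a text change and a little more modelling work. No new data or visits are needed, and the SAS version already named can fit the model. The model relies on a missing-at-random assumption, which the data cannot confirm.

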The synergistic BP-lowering effectiveness of acupuncture and antihypertensive agents has been proven, despite there formerly being insufficient evidence for acupuncture alone in lowering BP [22]. Recently, researchers have reported some positive results regarding sole acupuncture treatment for hypertension [23–25]. The reasons for this paradoxical situation could be disparities in acupuncture manipulation skills as well as other technical factors. Considering the limited reporting quality, the effect of pure acupuncture in lowering BP remains elusive.

Given that complementary and alternative interventions are recommended for mild and moderate hypertensive patients [26], we cautiously decided to select the hypertensive patients with uncontrolled BP (systolic BP ≥ 140 and < 160, or/and diastolic BP ≥ 90 and < 100 mmHg) who were taking one class of antihypertensive drugs to be the participants. The difference between the control and experimental groups is that in our experimental group, after a period of BP-lowering acupuncture add-on treatment, i.e., the “*HuoXueSanFeng*” needling method which has been proved to positively treat primary hypertension [27–33], if the BP falls below 140/90 mmHg, the prior antihypertensive drugs will be ceased, so as to observe the clinical effects of pure acupuncture on BP. Moreover, aiming to create a situation that is analogous to the real world, antihypertensive drugs will be adjusted based on the patients’ BP readings (detailed in the “Antihypertensive medication adjustment” section below) in both groups, respectively.

Altogether, our team conceived this high-quality, pragmatic randomized controlled clinical trial with the primary objective to determine whether BP-lowering acupuncture add-on therapy could decrease the recurrence of first-time ischemic stroke in patients during the 9-month follow-up period.

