### Antihypertensive medication adjustment

After randomization, an electronic BP machine and a BP diary notebook will be delivered to all patients for measuring and recording their BP levels. During the first 6-week inpatient treatments, they will be instructed how to use the machine accurately. BP will be measured within 1 h after morning waking before taking antihypertensive medications, at 3 h after taking antihypertensive medications, at 4 p.m. and before bedtime over the entire process. On each occasion, three repeated measurements of supine BP, following a rest of at least 15 min, will be conducted at 1-min intervals. The antihypertensive medication classes in both groups will be recorded. Lifestyle advice regarding hypertension and stroke will be given to the patients. In the experimental group, if the patients have a mean BP level below 140/90 mmHg for three consistent days, they will receive solely acupuncture treatment; thereafter, once their BP levels increase to ≥ 140 mmHg systolic and/or ≥ 90 mmHg diastolic for 1 month, prior antihypertensive medications should be re-dispensed. Otherwise, if BP levels are ≥ 160 mmHg systolic and/or ≥ 100 mmHg diastolic for three consistent days after initiating *HuoXueSanFeng* acupuncture treatments or over the follow-up period, additional antihypertensives should be prescribed. All the medication adjustments will be filled out in the Case Report Forms (CRFs).

For the control group, when the average systolic BP increases to ≥ 160 mmHg and/or diastolic BP ≥ 100 mmHg lasting for three continuous days in the study period, other antihypertensive drugs will be prescribed in the opinion of the treating physicians, and these will be documented for final analyses.

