The acupuncture method of *XingNaoKaiQiao* for the treatment of stroke was launched in 1972 by the first, and to date, only Chinese academician of engineering in the acupuncture discipline, [name], who devoted himself to introducing acupuncture to the whole world and developed an international academic team that cooperates with Germany, France, Japan, and Singapore, among other countries. For its internationally substantial contributions, *XingNaoKaiQiao* needling therapy for stroke has been recognized as another special acupuncture technique in addition to acupuncture anesthesia by foreign health care researchers. Besides the confirmed effects for stroke by our own team, the others also reported its encouraging results for stroke patients [38]. With the great success of *XingNaoKaiQiao*, academician [name] gained deeper insight into secondary stroke prevention, and established another acupuncture treatment for hypertension called *HuoXueSanFeng*, the BP-lowering acupuncture regimen used in our trial. Our previous researches have shown that this acupuncture method reduces BP for primary hypertension patients, and its immediate and long-term antihypertensive efficacy is significant for either BP-lowering or improving the patients’ clinical symptoms [27–33]. So, here we also want to investigate the BP-controlling effect of *HuoXueSanFeng*, especially regarding its sole efficacy, in a larger sample size population. In this study, both *XingNaoKaiQiao* and *HuoXueSanFeng* needling therapy are performed over the 12-week treatment period; *XingNaoKaiQiao* therapy is a general treatment for stroke with a high credibility, its free treatment here will enhance adherence with participation. Additionally, because both groups are needled, subject blinding should be ensured, minimizing the placebo effect of acupuncture.

Of note, in our trial, we cautiously selected three secondary endpoints, namely, Hcy, sCD40L, and copeptin levels, which were closely related to stroke recurrence. Elevated Hcy levels have been reported to be indicative of an increased risk for ischemic strokes and recurrent strokes [39]. sCD40L appears to be an independent predictor for stroke recurrence [40]. Copeptin has been studied to be a predictor of both severity at admission and 1-year stroke recurrence in stroke patients [41]. Assessing the influence of our study treatment on them might be reflective of the effects on stroke recurrence via acupuncture lowering hypertension.

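### The between-arm BP comparison mixes the acupuncture effect with a BP-triggered drug stop that applies in the experimental arm only, so it understates the add-on effect by an unknown amount and does not estimate the sole effect

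*Protocol article*

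**What the plan says.** **The drug rules.** Under Antihypertensive medication adjustment, in the experimental arm "if the patients have a mean BP level below 140/90 mmHg for three consistent days, they will receive solely acupuncture treatment". Once BP has been at or above 140 systolic and/or 90 diastolic for one month, "prior antihypertensive medications should be re-dispensed". The control arm has no stop rule. At or above 160 and/or 100 for three days, "other antihypertensive drugs will be prescribed in the opinion of the treating physicians, and these will be documented for final analyses"; the experimental arm has a step-up rule at the same threshold.

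**The purpose.** The Background says that "the prior antihypertensive drugs will be ceased, so as to observe the clinical effects of pure acupuncture on BP". The Discussion adds that "here we also want to investigate the BP-controlling effect of" HuoXueSanFeng, in particular on its own. Elsewhere the article calls the treatment an add-on.

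**The analysis.** Outcome assessments lists "Secondary endpoints, such as 24-h ambulatory BP", measured at baseline, week 6 and week 12. Sample size and statistical methods has diary BP compared at baseline, 2, 6 and 12 weeks, 6 months and 1 year: "We will compare between-group or within-group values at the indicated time points". It then fixes the method: "All the above different time-point assessments will be analyzed by repeated measures analysis of variance (ANOVA". It states no handling of drug stops, restarts or additions in the BP comparison, although all adjustments are recorded in the Case Report Forms.

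**The concern.** The endpoint itself triggers a treatment change, in one arm only, before the endpoint is next assessed. A patient whose BP falls on acupuncture loses the drug, and BP then rises by whatever the drug contributed. A control patient with the same fall keeps the drug. The more BP falls in the experimental arm, the more of its readings are taken off drug.

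The experimental mean is thus a mixture of acupuncture alone (patients whose BP fell) and acupuncture plus drug (the rest), set against drug alone.

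The article proposes lower BP as the route by which acupuncture reduces recurrence. A BP difference near zero could be read as evidence against that route when it partly reflects the stop rule.

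**Working it through.** **The plan's own figure.** No effect size, SD or sample size is given for BP. The only calculated figure, for stroke recurrence, reproduces. With 16% v 7%, two-sided 5% and 80% power: [1.960 × √(2 × 0.115 × 0.885) + 0.842 × √(0.16 × 0.84 + 0.07 × 0.93)]² / 0.09² ≈ 196.1, so 197 per group. Then 394 / 0.85 ≈ 464, within the 480 planned. This does not bear on BP.

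**Do the other stated methods remove the problem?**
- Per-protocol analysis: no. Stopping the drug follows the protocol.
- Last observation carried forward: no. Readings after the stop are observed, not missing.

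**Expected contrast.** Let A be the BP reduction from acupuncture on top of a constant drug, D the BP effect of the stopped drug, and f the share of the experimental arm off drug at the visit. Then:

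observed reduction = A − f × D; fraction lost = f × D / A.

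It is below A whenever f and D are positive, and reverses when f × D exceeds A. The documents give none of A, D or f, so all sizes below rest on assumptions.

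**Simulation 1.** Assumed: usual on-drug systolic BP about 148 mmHg (SD 6, limited to 140–160), daily SD 6, effect reached over two weeks, stop after three days each below 140, restart on a 30-day mean at or above 140, step-up at 160. Share of A lost at week 12:

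| A (mmHg) | D = 3 | D = 6 | D = 9 | D = 12 |
|---|---|---|---|---|
| 5 | 34% | 59% | 91% | 112% |
| 10 | 26% | 47% | 67% | 87% |
| 15 | 22% | 39% | 54% | 71% |

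The loss exceeds half in 7 of 12 cells. Check on one cell: for A = 10, D = 6, the simulated share off drug is 0.65, so withdrawal alone leaves 10 − 0.65 × 6 = 6.1. The simulated contrast is 5.3. The further 0.8 comes mainly from the step-up rule, which is the same in both arms but is met more often where BP is higher.

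**Simulation 2.** Assumed: usual on-drug systolic BP N(146, 8) with an entry reading of 140–159, daily SD 6, effect reached over four weeks, no step-up, A = 6. The wording leaves open whether a stop may recur and whether the one-month restart condition means every day or the average. Week-12 results:
- Repeated stops, restart on a 30-day mean: contrast −4.5, −3.2, −2.2, −1.3 mmHg for D = 3, 6, 8, 10 (25%, 47%, 63%, 78% lost).
- Repeated stops, restart only after 30 days each at or above 140: −2.2, −1.3, −0.5 for D = 6, 8, 10. Loss: (6 − 2.2)/6 = 63%, (6 − 1.3)/6 = 78%, (6 − 0.5)/6 = 92%.
- One stop only, restart on a 30-day mean, D = 6 to 10: about 8% lost at week 12, but about 42–63% at week 6.
- The highest loss over the readings tried is about 118%, a reversed sign.

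I re-ran the first two settings and obtained the same contrasts to within about 0.1 mmHg.

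**True effect zero.** The experimental arm then looks worse, by +0.3 to +3.6 mmHg over the readings tried, because day-to-day variation alone triggers some stops.

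Both simulations cover systolic BP over 12 weeks only. The 6-month and 1-year comparisons are not quantified.

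**The case against.** **The authors want off-drug readings.** The Background and Discussion say so, and the add-on effect on constant drug is not declared as the BP target. This stands: the fault is an undeclared target. But the planned contrast does not give the sole effect either, because patients who never met the stop rule remain on drug and the comparator is drug alone.

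**A strategy comparison is legitimate in a pragmatic trial.** This stands too. As an estimate of acupuncture plus BP-triggered drug changes against usual drug care, the contrast is valid. The article does not label it so.

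**The analysis plan may handle drug changes.** It is not shown and might. But the article fixes the method for all BP time points and states purposes which that contrast does not serve.

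**Most of the effect is cancelled, and ANOVA is to blame.** A reader might infer this. The documents do not support it. They give no effect sizes; the loss is below half in 5 of the 12 cells above and about 8% at week 12 under one reading of the rules. The cause is the one-sided rule with no declared target. Any model fitted to the same readings for the same contrast would inherit it.

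**The truncated model has limits.** It discards the off-drug readings and relies on early readings and on patients who never stopped. It recovered a true −6 mmHg as −5.97 on average, but in only 12 simulated trials, with no reported check under patient-varying effects or a wrong time course. It should therefore not carry every BP statement.

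**Conclusion.** The point holds in a limited form. The drug is stopped on low BP in the experimental arm only, and the planned between-arm BP comparison takes no account of it. Relative to the add-on effect, the contrast is pulled toward zero and can reverse; it is not an estimate of the sole effect.

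The direction was the same in every setting tried. The size is unknown: under assumed drug effects of 3 to 12 mmHg, acupuncture effects of 5 to 15 mmHg and several readings of the stop and restart rules, the loss by week 12 ranges from under 10% to over 100%. A statement that the plan removes most of the BP effect would go beyond the documents.

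The consequence is for interpreting a secondary endpoint: a null BP result would not show that acupuncture has no BP effect. The primary stroke comparison and its sample size are untouched. The change is worth making because it is cheap and alters what may be concluded about BP.

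**What to change.** Leave the drug rules as they are and change the analysis text in Sample size and statistical methods.

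1. State that the as-observed BP contrast (24-h ambulatory and diary) estimates the effect of the whole strategy, acupuncture plus BP-triggered drug changes, and that a null result is not evidence that acupuncture has no BP effect.
2. Pre-specify, as a supplementary estimate of the add-on effect, a likelihood-based mixed model of diary BP in both arms, with arm by time and a patient effect, using each patient's readings up to the first protocol drug stop or addition. State its assumptions: later values are missing at random given the recorded BP that triggers the change, and the time course is correctly modelled.
3. Report by arm, at each BP time point, the share of patients off drug and the share with an added drug. Present the off-drug readings separately, as a description of acupuncture alone rather than a randomized comparison.

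Cost: revised wording and one extra analysis, on diary and medication data already collected. The add-on estimate is model-dependent after the cut and makes no use of later readings from patients whose drug was stopped or supplemented.
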